## Abstract

**Introduction::**

An acute ST-elevation myocardial infarction (STEMI) is a very serious type of heart attack and a profoundly life-threatening medical emergency, and percutaneous coronary intervention (PCI) is the preferred strategy. However, in patients undergoing primary PCI, 30% to 40% may suffer the no-reflow phenomenon (NRP), and it could expand the myocardial infarction area and accompanied with high rehospitalization rate and fatality rate. In this study, we try to conduct a double blinded, randomized, placebo-controlled trial to observe whether the prophylactically intracoronary administration of Nicorandil could reduce the occurrence of NRP in STEMI patients undergoing PCI.

**Methods::**

Simple randomization in a 1:1 ratio will be made in blocks of variable size according to a random numbers generated by Excel 2010 to divide the patients to treatment group (Nicorandil) and control group (Saline). The outcomes are the occurrence of NRP, levels of interleukin-6 and HS-CRP, cTnT, and CK-MB before, and every 4 hours following PCI, and major adverse cardiovascular events at day 30. SPSS 23.0 (IBM, Chicago, IL) will be used, and *P*-value < .05 will be considered statistically significant.

**Conclusions::**

The findings will determine the efficacy of prophylactically intracoronary administration of Nicorandil to reduce the occurrence of NRP during PCI in acute STEMI patients.

**Trial registration::**

OSF Registration number: DOI 10.17605/OSF.IO/QPF3V

## Introduction

1

An acute ST-elevation myocardial infarction (STEMI) is a very serious type of heart attack and a profoundly life-threatening medical emergency, cause by the occlusion of 1 or more coronary arteries to result in myocardial injury or necrosis. Approximately 500,000 patients suffer STEMI annually,^[1]^ and it is estimated that STEMI comprises 25% to 40% of myocardial infarction presentation.^[2]^ Reperfusion therapy is reasonable for STEMI 12 to 24 hours within the onset. Percutaneous coronary intervention (PCI) is the preferred strategy, and it could rapidly re-canalize the infarct arteries, significantly reduce infarct area, and improve clinical outcome and long-term prognosis.^[3,4]^

However, in patients undergoing primary PCI, although without obvious dissection, thrombosis, spasm, or severe residual stenosis, 30% to 40% of patients may suffer the no-reflow phenomenon (NRP)^[5,6]^: after the recanalization of infarcted arteries, coronary blood flow to the ischemic tissue may still be impeded and the myocardial cell perfusion cannot be maintained. NRP is one of the common serious complications after PCI in STEMI patients, and it could expand the myocardial infarction area and accompanied with high rehospitalization rate and fatality rate.^[7–9]^

Many efforts have been made to prevent or reduce the occurrence of NRP, such as the administration of statins and Nicorandil.^[10–12]^ Nicorandil is an ATP-sensitive K^+^ opener, and it could dilate coronary artery to increase blood flow. Nicorandil has been administered in treating NRP in patients after PCI in some studies, and it may improve the symptoms of no-reflow in patient.^[13]^ However, there is still a lack of high quality randomized controlled trial to show the efficacy and safety of Nicorandil in preventing NRP during PCI in acute STEMI patients. In this study, we try to conduct a double blinded, randomized, placebo-controlled trial to observe whether the prophylactically intracoronary administration of Nicorandil could reduce the occurrence of NRP in STEMI patients undergoing PCI.

## Methods

2

### Study design

2.1

We will perform the double blinded, randomized, placebo-controlled trial (registration number: DOI 10.17605/OSF.IO/QPF3V) in Chongqing Dazu District People's Hospital from May April 1st, 2021 to April 31st, 2022. The protocol has been approved by the Health Research Ethics Board in the hospital. We will carry out the procedure in accordance with the Declaration of Helsinki. The flow of patients screening, randomization, and follow-up are presented in Figure 1.

**Figure 1 F1:**
[figure not shown]
Flow diagram of the study.

### Participants studied

2.2

Patients with sustained acute STEMI and suitable for PCI in hospital will be screened. Patients meeting the following criteria will be included:

(1)aging from 18 to 85 years old;(2)diagnosis of acute STEMI within 12 hours;(3)total occlusion of the infarcted artery;(4)blood pressure less than 90/60 mm Hg.

Patients with left bundle-branch block, kidney dysfunction, and histories of myocardial infarction, PCI, coronary artery bypass grafting will be excluded. Before randomization, all patients or authorized persons will sign a written informed consent, and they can freely choose whether to continue the trial at any time.

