### Outcome measures

2.5

The primary outcome is the occurrence of NRP defined as follows: thrombolysis in myocardial infarction flow grade less than 2 without dissection, spasm, or significant residual stenosis, at the end of interventional procedure, and a decrease of less than 50% of the basal elevation of ST segment at 90 minutes after reperfusion with PCI.

The secondary outcomes are levels of interleukin-6 and HS-CRP, cTnT, and CK-MB before, and every 4 hours following PCI, and major adverse cardiovascular events (postinfarction angina, reinfarction, heart failure, arrythmias, cardiogenic shock, and cardiovascular death) at day 30.

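### As worded, inclusion criterion 4 admits only patients below 90/60 mm Hg, which contradicts the stated target population and leaves the 30% control rate unsupported for those enrolled

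*Protocol article*

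**What the plan says.** All references are to the protocol article.

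- **Participants studied (2.2), screening:** "Patients with sustained acute STEMI and suitable for PCI in hospital will be screened". No blood-pressure limit is set at this step.
- **Participants studied (2.2), inclusion:** the list opens with "Patients meeting the following criteria will be included". Its four items are an age range, diagnosis within 12 hours, total occlusion of the infarct artery, and "blood pressure less than 90/60 mm Hg".
- **Participants studied (2.2), exclusion:** "Patients with left bundle-branch block, kidney dysfunction, and histories of myocardial infarction, PCI, coronary artery bypass grafting will be excluded". Blood pressure is not mentioned.
- **Introduction (1), aim:** to find out whether "prophylactically intracoronary administration of Nicorandil could reduce the occurrence of NRP in STEMI patients undergoing PCI". The abstract and the discussion state the same population.
- **Sample size (2.6):** 30% no-reflow under control against 15% on nicorandil, two-sided 5% level, 80% power, 118 per group and 280 in total. The control rate carries the same two citations as the introduction's figure of 30% to 40% for patients having primary PCI.
- **Outcome measures (2.5):** the day-30 composite includes "heart failure, arrythmias, cardiogenic shock, and cardiovascular death".

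**The concern.** An eligibility criterion is an operative rule: it decides who is randomised and to whom the result applies. This one, followed to the letter, turns away every STEMI patient whose pressure is not below 90/60 mm Hg. The trial would then inform only about a hypotensive subgroup, while its aim and conclusion speak of STEMI patients undergoing PCI.

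If the hospital's staff instead set the line aside as an obvious slip, every patient enrolled above the threshold breaches the published criterion, and the article misdescribes its own cohort. Neither course leaves eligibility, aim and sample-size assumption in agreement.

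**Working it through.** The point turns on the text, so most of the check is a comparison of sections. One figure can be reproduced.

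**1. Who is eligible as written.** Eligible = (age in range) and (STEMI within 12 hours) and (total occlusion) and (pressure below 90/60), less the listed exclusions. No exclusion concerns blood pressure, so everyone left is below 90/60.

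**2. Who would be eligible under either plausible slip.** Suppose the inequality was reversed, or the line belongs with the exclusions. In both cases, at the same threshold, patients below 90/60 could not enter. The literal population and the population under either slip therefore share no patients. The choice of reading changes the whole cohort and not just its edges.

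**3. Which reading the rest of the article fits.**
- Aim, conclusion and discussion: STEMI patients undergoing PCI, with hypotension never mentioned.
- Screening sentence: STEMI and suitable for PCI, with no pressure limit.
- Limitations in the discussion: a single centre, and the lack of quantitative cardiac imaging. A deliberate restriction to hypotensive patients would be expected here and is absent.

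No section supports a hypotensive-only trial apart from the criterion itself.

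**4. The sample size.** Inputs from section 2.6: p1 = 0.30, p2 = 0.15, two-sided alpha 0.05, power 80%, allocation 1:1. With the unpooled normal approximation:

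n = (1.960 + 0.842)² × [p1(1 − p1) + p2(1 − p2)] / (p1 − p2)²

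= 7.849 × (0.2100 + 0.1275) / 0.0225 = 117.7, so 118 per group.

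This matches the stated figure. The pooled version gives 121. The arithmetic is therefore sound for the rates assumed, and blood pressure does not enter the formula. What the criterion affects is whether p1 = 0.30 describes the patients enrolled. That rate is reported for primary-PCI patients in general. The article gives no rate for patients below 90/60, so n cannot be recalculated for the population that the criterion literally defines.

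**5. The composite outcome.** If all patients are hypotensive at entry, a shock event by day 30 may be harder to tell from the state at baseline. This is a possible overlap and not a demonstrated one, since the article does not define shock by a pressure cut-off.

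**The case against.** **It is plainly a drafting slip, and everything else points to general STEMI patients.** That is probably so, and it limits the claim. A reader might infer that the trial cannot answer its question at all. That follows only if the line is applied literally, and the article does not show how screening is done in practice (the flow diagram is not available). But calling it a slip concedes that the text needs correcting, and the text does not reveal which slip occurred. Nor is this detail that a short article leaves to a fuller document: a criterion is stated, and it conflicts with the sections around it.

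**The 30% rate may still be right.** This stands. A reader might infer that the sample size is wrong. The article shows only that the rate is unsupported for a hypotensive cohort. It could be higher, lower or the same.

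**Cardiogenic shock as an outcome is not a contradiction.** This also stands. A patient below 90/60 is not necessarily in shock, and a hypotensive cohort can still develop it. Only the possibility of overlap remains.

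**A safety failure might be inferred,** namely that the trial enrols the very patients it meant to protect. The article does not support this. It says of nicorandil that "it could dilate coronary artery to increase blood flow", says nothing about systemic pressure, and names no group to be protected on that ground.

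**Infeasible recruitment might also be inferred.** The article gives no share of STEMI patients below the threshold, so no screening burden can be derived from it.

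**Conclusion.** The criterion is wrong as written, or else the aim and the control rate are. As worded, only patients below 90/60 mm Hg may enter. That contradicts the target population in the abstract, introduction and discussion, and it separates the enrolled cohort from the one that supplied the 30% control rate.

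All 280 planned patients are affected, because the literal rule and its likely intended forms select disjoint groups. The numerical effect on power is unknown: 118 per group reproduces at 30% against 15%, and no rate for hypotensive patients is given. The overlap with cardiogenic shock is a secondary and tentative point.

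The conclusion rests on reading the inclusion list in its ordinary sense, with all four items required, and on no other available section qualifying item 4. It does not depend on any clinical judgement about which blood-pressure rule is right.

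**What to change.** Before enrolment, reconcile criterion 4 with the stated objective, the exclusion list and the source of the control rate. The blood-pressure rule, and the list it belongs in, are for the sponsor to decide; the document does not settle either.

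If the line is a slip, the cost is a one-line protocol amendment and a matching correction to the published text. The sample-size inputs need no change on this account.

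If a hypotensive-only population is really intended, restate the title, aim and conclusion for that population and justify the control rate for it, recalculating the sample size if the rate differs. It should then also be made clear how shock arising after entry is told apart from the baseline state. That is more work, but without it the result could not be read against the question the article asks.

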### Randomization and blinding

2.3

Simple randomization in a 1:1 ratio will be made in blocks of variable size according to a random numbers generated by Excel 2010 to divided the patients to treatment group (intracoronary injection of 2 mg Nicorandil) and control group (intracoronary injection of 2 mL Saline). The attending physician, patients, outcome evaluators, and statistical analysts will be blinded to the allocation. To maintain blinding, Nicorandil and Saline are in the same package and appearance.

### Interventions

2.4

All patients in both groups will take antiplatelet drugs including 300 mg Aspirin (Bayer, Germany) and 600 mg Clopidogrel (Sanofi [Hangzhou] Pharmaceutical Co., Ltd, Hangzhou, China), and Heparin (70 U/kg) will be injected through the artery sheath tube before PCI.

In the treatment group, 2 mg Nicorandil (Beijing Sihuan Kebao Pharmaceutical Co. Ltd, Beijing, China) will be injected 2 mm distal to the site of the occlusion in the coronary artery in the thrombus-aspiration catheter. Angiography will be repeated 5 minutes later to determine whether to repeatedly administer 2 mg Nicorandil. The total dose of Nicorandil should not exceed 6 mg in any patients.

In the control group, 2 mL Saline (Tianjin Barence Biotechnology Co., Ltd, Tianjin, China) will be injected 2 mm distal to the site of the occlusion in the coronary artery in the thrombus-aspiration catheter. Angiography will be repeated 5 minutes later to determine whether to repeatedly administer 2 mL Saline. The total dose of Nicorandil should not exceed 6 mL in any patient.

### Outcome measures

2.5

The primary outcome is the occurrence of NRP defined as follows: thrombolysis in myocardial infarction flow grade less than 2 without dissection, spasm, or significant residual stenosis, at the end of interventional procedure, and a decrease of less than 50% of the basal elevation of ST segment at 90 minutes after reperfusion with PCI.

The secondary outcomes are levels of interleukin-6 and HS-CRP, cTnT, and CK-MB before, and every 4 hours following PCI, and major adverse cardiovascular events (postinfarction angina, reinfarction, heart failure, arrythmias, cardiogenic shock, and cardiovascular death) at day 30.

### Sample size

2.6

As previous literature reports, the occurrence of NRP was over 30%.^[5,6]^ We preliminarily found that Nicorandil could reduce the occurrence to 15%, and taking α = 5%, 1-β = 80% with a 2-sided test, 118 cases will be calculated in each group. Considering a potential dropout of 20% in the 30-day-follow-up, 280 cases will be needed in total.

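### The enrolment total of 280 does not follow from 118 per group and a 20% dropout allowance; the matching total is 296

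*Protocol article*

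**What the plan says.** All the inputs stand in section 2.6 (Sample size) of the protocol article. The control rate comes from earlier literature, in which "the occurrence of NRP was over 30" per cent. The treatment rate comes from the investigators' own preliminary work: "We preliminarily found that Nicorandil could reduce the occurrence to 15" per cent. The error rates are given as "taking α = 5%, 1-β = 80% with a 2-sided test". From these the article concludes that "118 cases will be calculated in each group", and then adds the attrition allowance: "Considering a potential dropout of 20% in the 30-day-follow-up, 280 cases will be needed in total".

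Two other sections bear on the point. Section 2.3 (Randomization and blinding) sets the allocation as "Simple randomization in a 1:1 ratio". Section 2.5 (Outcome measures) makes no-reflow the primary outcome. It is judged partly on flow at the end of the procedure and partly on ST-segment recovery, specified as "a decrease of less than 50% of the basal elevation of ST segment at 90 minutes after reperfusion with PCI". Day 30 is the time point for major adverse cardiovascular events (MACE), a secondary outcome.

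**The concern.** An attrition allowance is meant to leave the calculated number of evaluable patients after the expected loss. Here the calculated number, the expected loss and the enrolment total are all stated, and the total is too small for the other two. The enrolment total is a figure that the trial and its readers rely on. If it does not follow from its own inputs, a reader cannot tell which of the three the investigators mean to stand by, or how much loss the trial can absorb.

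**Working it through.** **Inputs.** From section 2.6: control rate p1 = 0.30 (the article says over 30%, so this is the lower end), treatment rate p2 = 0.15, two-sided α = 0.05, power 0.80, 20% dropout, total 280. From section 2.3: 1:1 allocation.

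**Step 1: reproduce the 118.** The normal approximation with unpooled variance is

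n per group = (z₀.₉₇₅ + z₀.₈₀)² × [p1(1−p1) + p2(1−p2)] / (p1−p2)²

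= (1.960 + 0.842)² × (0.2100 + 0.1275) / 0.15² = 117.7, rounded up to 118.

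The stated 118 reproduces exactly. The pooled-variance version gives 121, which is close. The base figure is sound, and the fault lies in the next step.

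**Step 2: apply the dropout allowance.**

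- Evaluable total: 2 × 118 = 236.
- Enrolment for 20% loss: 236 / (1 − 0.20) = 295. Per group, 118 / 0.80 = 147.5, rounded up to 148, so 296 in total.
- Multiplying by 1.2 instead, a common mistake, gives 236 × 1.2 = 283.2, rounded up to 284. The stated 280 is close to this but below it, so it does not satisfy that rule either.

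**Step 3: what 280 provides.**

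- Retained after 20% loss: 280 × 0.80 = 224, or 112 per group, which is 118 − 112 = 6 per group short.
- Largest loss that still leaves 236: 1 − 236/280 = 15.7%.
- Enrolment shortfall: 296 − 280 = 16 (15 against 295), about 5%.

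**Step 4: consequence for the primary outcome.** With the formula that gives the 118,

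power = Φ( 0.15 / √(0.3375/n) − 1.960 )

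| Evaluable per group | When this applies | Power, unpooled formula | Pooled formula | Exact, uncorrected χ² |
|---|---|---|---|---|
| 112 | the full 20% also lack the 90-minute outcome | 78.0% | 77.0% | 77.5% |
| 118 | the stated requirement | 80.1% | 79.2% | 79.8% |
| 140 | all 280 have the 90-minute outcome | 86.3% | 85.6% | 86.0% |

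By the unpooled formula, power for no-reflow stays at about 80% or more unless more than 15.7% of patients lack the 90-minute outcome.

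**Step 5: sensitivity to the control rate.** At 112 per group and 15% on Nicorandil, the same formula gives about 80% power for a control rate of 30.5% and about 83% for 31%. The 78% therefore needs a control rate of exactly 30%, the lowest value compatible with the article's wording.

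**The case against.** A reader might infer that the trial fails to deliver its stated 80% power, and that dropout, size and power are mutually incompatible. The document does not support that. The article ties the 20% to the 30-day follow-up, whereas the last component of no-reflow is measured 90 minutes after reperfusion. A patient who is lost between discharge and day 30 already has a primary outcome. An enrolment of 280, a 20% loss by day 30 and at least 80% power for no-reflow can all be true together.

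The Fisher exact test, which section 2.7 also lists, might seem to make the power loss larger: 72.7% at 112 per group. But Fisher already gives only 75.4% at 118 per group, so most of that gap comes from changing the test rather than from dropout.

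The timing argument stands, and it removes any firm claim of low power. It does not rescue the 280. Section 2.6 applies the 20% directly to the number calculated for no-reflow, and this is the only inflation step in the article. No smaller loss for the 90-minute outcome is stated, so the 86% is a reasonable inference and not something the plan says. If the 20% has no bearing on the primary outcome, the inflation has no basis there. For day-30 MACE, where the 20% does apply, 280 still leaves 224 and not 236. Nor is this a matter of a condensed article: every input and the result are printed, and no further detail could make 236, 20% and 280 agree.

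**Conclusion.** The point holds as a minor arithmetic inconsistency. The 118 per group is correct for its stated assumptions, but 280 does not carry a 20% allowance on it. The matching total is 295, or 296 with equal arms, and 280 supports a loss of at most 15.7%.

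The practical effect is small. As stated, the shortfall falls mainly on day-30 MACE, for which the article claims no power. For no-reflow, power is about 86% if all 280 are evaluable. The worst case, with the full 20% missing at 90 minutes, is about 78% by the planning formula, roughly 2 points below the 80.1% at 118 per group. These power figures assume a control rate of exactly 30%, a treatment rate of 15% and equal loss in the two arms. The size of the arithmetic error itself depends on none of these.

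**What to change.** Restate the last sentence of section 2.6 so that its figures agree. There are two ways to do this without enrolling more patients:

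- Keep 280 and state that it tolerates about 15% loss (236 / 0.85 = 277.6, so 278).
- State the loss expected for the 90-minute primary outcome, justify 280 on that basis, and describe the 30-day loss separately as applying to MACE.

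If 20% is to remain the allowance on 118 per group, the total should read 296, which is 16 more patients.

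Keeping both 280 and 20% and quoting a power of 77–78% would not be a good repair, because it would charge the primary outcome with losses that occur after it has been measured.

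Either of the first two options costs one sentence; the first also means printing a slightly less favourable dropout allowance. Design and analysis are unchanged.

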### Statistical methods

2.7

Data with a normal distribution will be expressed as mean ± standard deviation, and categorical data as percentages. Student *t* test, Wilcoxon rank-sum test, Mann–Whitney *U* test, *χ*^2^ test, or Fisher exact test will be applied accordingly. SPSS 23.0 (IBM, Chicago, IL) will be used, and *P* < .05 will be considered statistically significant.

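### The sample size for a 90-minute primary outcome is enlarged for 30-day dropout, and the stated 80% power, 20% loss and 280 patients do not fit together

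*Protocol article*

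**What the plan says.** All references are to the protocol article.

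- **Section 2.6, Sample size.** The calculation is driven by NRP. The control rate comes from earlier literature ("the occurrence of NRP was over 30" per cent) and the treated rate from the authors' preliminary findings ("Nicorandil could reduce the occurrence to 15" per cent). The error rates are set by "taking α = 5%, 1-β = 80% with a 2-sided test". The result is "118 cases will be calculated in each group". An allowance follows, "Considering a potential dropout of 20% in the 30-day-follow-up", and the conclusion is that "280 cases will be needed in total".
- **Section 2.5, Outcome measures.** NRP has an angiographic part, read when the procedure ends, and an ECG part, read "at 90 minutes after reperfusion with PCI". Nothing later enters its definition. MACE is a secondary outcome and the only one tied to day 30.
- **Section 2.7, Statistical methods.** A general list of tests closes with "Fisher exact test will be applied accordingly". It links no test to a named outcome and defines no analysis set.

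**The concern.** The attrition rate and the outcome it is applied to belong to different time frames. Patients who drop out in the weeks after the procedure cost the trial MACE information, but they cost it nothing on NRP, which was settled within hours of arrival. The loss that matters for the primary outcome is the loss before the 90-minute reading: a missing ECG, an early death or an early withdrawal. Section 2.6 gives no figure for it.

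Two things are at stake. First, the reader cannot tell what power the trial has for its primary comparison, because the one loss rate given does not describe that comparison. Second, section 2.6 is the only text that bears on how many patients count towards the primary result. Left as it stands, it could be taken to mean that later dropouts are not expected to contribute to NRP.

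**Working it through.** **Inputs.** p1 = 0.30 and p2 = 0.15 (section 2.6; 0.30 is the lower edge of the stated control rate); two-sided α = 5%, so z = 1.960; power 80%, so z = 0.842; 1:1 allocation (section 2.3); dropout 20%; total 280.

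**Step 1: reproduce 118.** Unpooled normal approximation:

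n = (1.960 + 0.842)² × [0.30 × 0.70 + 0.15 × 0.85] / (0.30 − 0.15)² = 7.849 × 0.3375 / 0.0225 = 117.7, so 118 per group and 236 in total.

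This matches the article. The pooled-variance formula gives 121, so 118 is sound to within the choice of formula.

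**Step 2: reproduce 280.**

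- Multiplying up: 236 × 1.2 = 283.2. The stated 280 is close to this, rounded down.
- Dividing by the fraction retained: 236 / 0.8 = 295 (296 in equal groups). The stated 280 is not close to this.
- The loss that 280 can bear with 236 remaining: 1 − 236/280 = 15.7%.

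So 280 is short of a 20% allowance even on its own terms: 280 × 0.8 = 224, not 236.

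**Step 3: power for NRP according to the loss before 90 minutes.** Pooled two-proportion test, with mean rate 0.225:

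power = Φ{[0.15√n − 1.960 × √(2 × 0.225 × 0.775)] / √0.3375} = Φ{(0.15√n − 1.1575) / 0.5810}

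| Loss to NRP, of 280 | n per group | Argument of Φ | Power |
|---|---|---|---|
| 0% | 140 | (1.7748 − 1.1575)/0.5810 = 1.063 | 85.6% |
| 5% (assumed) | 133 | (1.7299 − 1.1575)/0.5810 = 0.985 | 83.8% |
| 10% (assumed) | 126 | (1.6837 − 1.1575)/0.5810 = 0.906 | 81.7% |
| 15.7% | 118 | (1.6294 − 1.1575)/0.5810 = 0.812 | 79.2% |
| 20% | 112 | (1.5875 − 1.1575)/0.5810 = 0.740 | 77.0% |

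Exact enumeration of the uncorrected chi-square test gives nearly the same values: 86.0% at 140 per group, 79.8% at 118 and 77.5% at 112.

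**Step 4: set against the plan.** If the 20% applies to NRP, 280 misses the 80% target. If it does not, 280 exceeds the 236 needed for NRP by 44 and the power is nearer 86%. On neither reading do 80%, 20% and 280 belong together.

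**MACE.** A 20% loss leaves 280 × 0.8 = 224 patients with complete day-30 follow-up and 56 without. Power for MACE cannot be computed, because the article gives no MACE rate.

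**The case against.** The best defence is that a recruitment margin is not an exclusion rule. Section 2.6 only enlarges enrolment, and no section removes anyone from the NRP comparison. If the margin is more than NRP needs, the trial is somewhat better powered than claimed, which does no statistical harm. Some allowance is defensible anyway: section 2.2 lets patients stop at any time, a 90-minute ECG can be missed, and a sponsor may reasonably choose a total that also covers the day-30 outcome.

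Most of this stands, and it limits the point. A reader might infer that NRP will be analysed only in patients who complete 30 days, with 9 points of power lost (86% to 77%) and the randomised comparison broken. The article does not say so; the inference rests on the dropout sentence alone, and analysis sets are commonly left to the full protocol or the SAP.

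A reader might also infer that MACE is wrongly analysed because section 2.7 offers only chi-square and Fisher tests for categorical data. That does not hold either. No test is assigned to MACE, and either test is valid for a yes/no outcome at a fixed day. Events seen before loss can still be counted, and the handling of missing follow-up is normally SAP detail. Censoring in a time-to-event analysis would not cure loss that is related to prognosis.

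The defence does not rescue the figures. The article states a power, a loss and a total that cannot all be right for the outcome on which the trial is sized.

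**Conclusion.** The point holds as an error in the stated sizing. A 30-day loss is charged to an outcome complete at 90 minutes, and 280 is not the total that a 20% loss would require (295). The power for NRP lies between about 77% (20% lost before 90 minutes) and about 86% (none lost). On the pooled formula it stays above 80% with up to about 10% early loss.

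The practical effect is modest. Early loss well below 20% seems likely for an in-hospital reading at 90 minutes, though the article gives no figure, and in that case the trial is adequately powered as planned. The calculation rests on the article's own rates of 30% and 15%. With the treated rate held at 15%, a control rate above 30% would raise every power figure.

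No bias in the NRP comparison and no error in the MACE analysis is established by this text.

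**What to change.** In section 2.6:

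- State the loss expected for NRP itself, from missing 90-minute ECGs and from deaths or withdrawals before that reading.
- Restate the power of 280 on that basis: about 86% if that loss is nil, about 77% if it is 20%, with the table above for values between.
- Attach the 20% allowance explicitly to day-30 MACE.

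In section 2.7, add that patients lost after the 90-minute reading remain in the NRP comparison, in the arm to which they were assigned.

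The cost is a few sentences and no extra patients. If the sponsor does expect 20% to lack an NRP result and wants to keep 80% power, the total should instead be 295 (296 in equal groups).

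A time-to-first-event analysis of MACE could be added as a sensitivity analysis if the dates of first event and last contact are recorded. It is optional and corrects no error.
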